### Secondary outcomes

#### Independence function and muscle strength

The effects of VR at the level of activity will be investigated. The Functional Independence Measure (FIM) is one of the secondary outcomes, which aims to quantify and measure whatever the individual personally achieves (28). It consists of 66 points, with lower scores denoting more severe UE impairment and greater scores suggesting better motor function gains. The Barthel Index (BI) is considered to measure independence in activities of daily living (ADLs) (29). It has a 100-point scale, with lower scores denoting serious ADL interdependence and higher scores suggesting improved ADL independence. A hydraulic Jamar hand dynamometer was used to measure the maximum grip strength. This was kept according to the protocol of the American Hand Therapy Association (30).

### Imaging outcomes

Secondary outcomes will be obtained through the use of rs-fMRI and ts-fMRI, which will be assessed to identify changes in the BOLD effect in ipsilesional and contralesional M1 on the left and right hemispheres, and also EEG. The MRI scanner is a 3.0T Philips (Philips Achieva, Philips, Medical Systems, Best, Netherlands) superconducting MRI system, and the coil used for scanning is a standard 32-channel head coil. Each subject will be laid supine, with the head in a neutral posture and secured with a belt and foam pads during the test. The scanning parameters are as follows: rs-fMRI: echo-planar imaging (EPI), the 46 layers of transverse fault, a layer of thickness of 2.5 mm, a layer spacing of 0.5 mm, the repetition time (TR) of 2,000 ms, the echo time (TE) of 20 ms, a tilt angle of 90°, the field of view (FOV) of 240 mm × 240 mm, and an acquisition matrix of 96 × 96. After the resting function scan, the task function scan under the same parameters will be performed, and the subject will be stimulated by the motion observation task during the ts-fMRI test.

A brain function audio-visual stimulation system (Samrtec SA-9900, Shenzhen Meide Medical Electronics Technology Co., Ltd., China) will be used to display the stimulation images, which should ensure synchronization between the picture stimulation task and scanning. The hemiplegic hand will be used by the subjects to make the conventional whole-hand fist closures. On the video screen, written instructions will be given for 2 s, instructing individuals to move the hemiplegic hand. The instruction text will be replaced with a black circle on a white screen that has begun blinking red at a rate of 2 Hz after a randomly jittered delay of 1.5–2.5 s. Subjects will be told to make fist closures at the same frequency that the red circle appeared.

The hands will move in full finger flexion and extension at the frequency of the visual cue while both hands are resting in a supine position on cushions next to the hips. After 30 s, the circle vanishes, and a white screen will instruct the subjects to put their hands down for ~30 s before the start of the following block of motions. In total, five stimulus events and four periods of resting time will total 270 s in each fMRI test.

Before scanning, subjects will undergo task familiarization training until a steady performance is attained. Patients who are unable to execute at the necessary frequency will be told to perform as closely as they can to the visual cue while maintaining proper fist opening and closing.

EEG detection (power spectrum and scalp function connection) will be carried out by Cadwell easy-type III EEG (Cadwell, Washington, USA) produced by Kaiwei Company in the United States. The participants will sit in a comfortable chair and wear an EEG hat that will be connected to the Cadwell Easy III recording system. EEG data will be recorded at a sampling rate of 500 Hz from 17 silver electrodes of Fp1, Fp2, F3, F4, F7, F8, T3, T4, C3, C4, Cz, T5, T6, P3, P4, O1, and O2, and the other two reference electrodes will be connected to the left and right auricles. Each electrode is filled with an electrode gel (Weaver and Company, Colorado, USA) produced by Weaver Medical Technologies to ensure good electrical contact between the electrode and the skin. The electrode impedance is maintained below 10 kΩ. During the experiment, participants will be instructed to keep their arms and hands relaxed. Throughout the experiment, the actual execution of hand movements will be prohibited due to large individual variations in the participants' level of motor control, and the information will be saved on a computer for further offline processing.

### Safety evaluation and adverse events

This method does not affect the normal physiological state. Tests for safety indicators before and after treatment include general physical examination (blood pressure, pulse, and respiration), electrocardiogram, blood routine, urine routine, stool routine, and liver and kidney function tests. Adverse events such as pain, dizziness, local infections, allergies, and seizure will be meticulously documented in the case report form (CRF). Serious negative events, such as fatalities or situations posing a serious risk to one's life, will be notified right away to the researcher and to the ethics committee within 24 h. The visual analog scale (VAS) will be assessed before and after intervention training and after fMRI and EEG to grade sleepiness, fatigue, and anxiety (31). In this case, the research team will give the patient treatment and recommendations based on the situation, evaluate whether he/she could continue to participate in the study, and award compensation in accordance with that decision.

### Data management

Skilled assessors will utilize CRFs to precisely collect patient data and information before importing them into an electronic database. The paper CRFs will be maintained in a locked cabinet when the study is finished. Researchers never change the data because it has already been secured in the electronic database as well. Personal information about participants will be kept anonymous and under tight confidentiality. With their approval, we will collect patient data over the phone for those who drop out or withdraw from the study in the experiment.

### Data analysis

Data analysis will be performed using SPSS software (IBM, Statistics 25 version). Measurement data that follow a normal distribution as a whole will be expressed as mean ± standard deviation (X ± SD), and the whole data will not follow a normal distribution in median (interlude spacing) [M(P25–P75)]. The count data will be expressed as the number of cases (composition ratio) [*N*, (%)], and the analysis is tested by the *X*^2^ or Fisher's exact tests precisely. The comparison between the groups will be carried out by the *t*-test or the Mann–Whitney *U*-test based on whether the measurement data present a normal distribution and homogeneous variance to compare the differences in FMA-UE and independent sample *t*-test for the parameter in FIM, BI, grip strength, fMRI and EEG at a *p*-value below 0.05. There are no interim analyses planned.

fMRI image processing will use the statistical parameter graph software statistical parametric mapping (SPM)12. Before data processing, all data will be adjusted in orientation; and then head-action alignment, high-resolution structural image, and the average functional image will be registered; the high-resolution structural image after registration will be split; all the aligned functional images will be standardized to the Montreal Neurological Institute space using the standardized parameters generated during the segmentation process; the standardized voxel size is 3 mm × 3 mm × 3 mm; and the standardized functional image is spatially smoothed. Through an intragroup analysis, a paired *t*-test will be performed to assess brain alterations in each group (before and after the treatment). Age and gender will be taken into account as variables in the data analysis. The association between the improvement value of the correlation scales and the change in fMRI image data will be examined using the Pearson correlation coefficient.

For pre-processing and analysis, EEG data will be exported to MATLAB 9.2.0 (MathWorks, Inc., Natick, MA). A second-order Butterworth filter with a bandpass of 0.1–70 Hz and a band stop of 49–51 Hz will be used to filter the data. The data will be divided into 90 segments of 2 s each, and epochs with obvious artifacts will be removed by visual inspection. To find and eliminate non-physiological artifact components, data will be subsequently subjected to an independent component analysis using the EEGLAB rapid independent component analysis (ICA). The missing channels will be interpolated after the artifacts will be removed. The frequency domain indicators will be extracted and counted, Fourier transform on the preprocessed data will be performed and converted into a power spectral density (PSD) in decibels, each frequency band of interest will then be exported, the power value will be calculated, statistical analysis will be performed, and the difference will be output into the document.

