**Methods/design:**

In this single-center, randomized, parallel-group clinical trial with a blinded assessment of outcomes, a total of 78 stroke patients will be assigned randomly to either the VR group or the control group. All stroke patients who have upper extremity motor deficits will be tested with functional magnetic resonance imaging (fMRI), electroencephalography (EEG), and clinical evaluation. Clinical assessment and fMRI will be performed three times on each subject. The primary outcome is the change in performance on the Fugl-Meyer Assessment Upper Extremity Scale (FMA-UE). Secondary outcomes are functional independence measure (FIM), Barthel Index (BI), grip strength, and changes in the blood oxygenation level-dependent (BOLD) effect in the ipsilesional and contralesional primary motor cortex (M1) on the left and right hemispheres assessed with resting-state fMRI (rs-fMRI), task-state fMRI (ts-fMRI), and changes in EEG at the baseline and weeks 4 and 8.

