### Outcome measures

Participants will be evaluated at baseline and weeks 4 and 8. All evaluations will be conducted by researchers who will be blinded to the treatment allocation.

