### Primary outcome

The primary outcome is the FMA-UE, which has been developed as an evaluative measure of the upper limb functionality recovery poststroke (25–27). The FMA-UE score is 66 points, with lower scores indicating more severely impaired UE and higher scores indicating better motor function improvements. The baseline assessment results of this study are recorded as FM0, the second assessment results are carried out as FM1 after interventions, and the follow-up assessment results are recorded as FM2.

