### Quality control

The reasons for the suspension of the study and the relationship between the clinical study should be carefully recorded, and the criteria for the suspension of clinical research should be stipulated. When the subject will suspend the clinical study, the corresponding clinical evaluation will be carried out, and the statistical processing principle of the data after the suspension of the clinical study will be determined. For the subject who proposes to withdraw from the clinical study in the middle, the reason should be clearly recorded, if the subject will not be followed up on time, the reason should be consulted by telephone or letter, and the situation after the study will be investigated, and the clinical evaluation of the subject when withdrawing from the clinical study will be carried out.

In order to make this project function smoothly, the relevant operating procedures of clinical research and the implementation process will be scientifically and rigorously standardized. Researchers will be trained uniformly to master the implementation of interventions in the intervention group and the control group so as to improve the internal observation consistency and observer-to-observer consistency of researchers and ensure the reliability of clinical research conclusions. Quality monitors will be set up to carry out quality control and supervision of the whole process of research, the records and reports of all research data will be checked and confirmed, and the correctness and completeness of the case report will be formed, and it will be ensured that they are consistent with the original data. The trial review team consists of two staff members from the review department and will be responsible for a regular review of progress, authenticity, and safety every 12 weeks. Trial audit teams, independent data monitoring, and ethics committees must review the conduct throughout the trial.

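### A free improvement: adjust the primary FMA-UE comparison for baseline FMA-UE by ANCOVA, instead of an unadjusted t-test or Mann-Whitney test picked from the trial's own data

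*Protocol article*

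**What the plan says.** The abstract (Methods/design) states: "The primary outcome is the change in performance on the Fugl-Meyer Assessment Upper Extremity Scale (FMA-UE". The Primary outcome section labels the measurements: "The baseline assessment results of this study are recorded as FM0, the second assessment results are carried out as FM1 after interventions"; the follow-up value is FM2. Under Outcome measures, "Participants will be evaluated at baseline and weeks 4 and 8", and Table 1 schedules FMA-UE at all three times, so FM0 is planned for everyone.

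The Data analysis section names the between-group test for FMA-UE as a t-test or a Mann-Whitney U-test, selected "based on whether the measurement data present a normal distribution and homogeneous variance to compare the differences in FMA-UE", and gives an independent-samples t-test for FIM, BI, grip strength, fMRI and EEG, all "at a *p*-value below 0.05". It names no baseline term for FMA-UE. The only covariates mentioned anywhere are in the fMRI paragraph of the same section: "Age and gender will be taken into account as variables in the data analysis". That sentence does not name FM0.

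**The concern.** Baseline FMA-UE is likely to be among the strongest predictors of later FMA-UE, and it costs nothing extra to use. A two-sample test without it has two consequences. The standard error is larger than it need be. A baseline difference that arises by chance also carries over in part to the estimated effect: upwards into a comparison of follow-up scores, and downwards, through regression to the mean, into a comparison of change scores.

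The selection rule raises a second issue. If the observed data look non-normal or the variances differ, the primary result changes from a difference in means to a comparison of ranks. These are different quantities, and which one the trial reports would be settled only after the data are seen. Mann-Whitney is not a remedy for unequal variances either, yet unequal variance is one of the triggers for using it.

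**Working it through.** **Inputs from the article.** Effect size f = 0.25, which for two groups is d = 2f = 0.50; power 0.80; 65 evaluable; 15% dropout; 78 enrolled (Sample size). Significance level 0.05 (Data analysis). 

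**Assumptions.** Two-sided test, 1:1 allocation, equal SD at baseline and follow-up, and a baseline to follow-up correlation r, for which the article gives no value. I use r = 0.5, 0.7 and 0.8. Since 78 × 0.85 = 66.3, I take 66 evaluable, 33 per arm.

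**The article's own figure.** A two-group t-test at d = 0.5 and two-sided 0.05 has power 0.51 with 65 patients, and needs 128 for power 0.80. So the stated 65 does not reproduce for the test named in Data analysis. That is a separate sample-size matter; it is noted here only because it fixes the starting level of power. The dropout step does hold: 65 / 0.85 = 76.5, so 77, or 78 as an even number.

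**Precision.** Relative to the variance of the raw score, the variance of the compared quantity is:
- follow-up score: 1
- change score: 2(1 − r)
- ANCOVA on FM0: 1 − r²

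The ratio of ANCOVA to change score is (1 − r²) / [2(1 − r)] = (1 + r)/2. ANCOVA therefore has the smallest variance of the three for any r strictly between 0 and 1.

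**Power, d = 0.5 in SDs of the score.** Noncentrality is 0.5 × √(66/4) / √(variance factor) = 2.031 / √(variance factor).

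| r | follow-up score | change score | ANCOVA |
|---|---|---|---|
| 0.5 | 0.52 | 0.52 | 0.64 |
| 0.7 | 0.52 | 0.73 | 0.80 |
| 0.8 | 0.52 | 0.89 | 0.92 |

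Example at r = 0.7: the factors are 0.60 and 0.51, so noncentrality is 2.62 for the change score and 2.84 for ANCOVA.

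**Power, d = 0.5 in SDs of the change score.** The t-test on change has 0.52 at every r. ANCOVA, with factor (1 + r)/2 = 0.75, 0.85, 0.90, has 0.64, 0.58 and 0.56.

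**Chance imbalance.** The SE of the baseline difference at 39 per arm is √(2/39) = 0.226 SD. An imbalance of 1 SD moves the follow-up comparison by +r SD and the change comparison by −(1 − r) SD. For an imbalance of one SE at r = 0.7, that is 0.7 × 0.226 = +0.16 SD for follow-up scores and −0.3 × 0.226 = −0.07 SD for change scores, against a target of 0.5 SD. ANCOVA removes the linear part of this.

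**Test selection.** The choose-then-test rule was simulated under no effect with 33 and 32 patients (Shapiro-Wilk in each arm and Levene, then t-test or Mann-Whitney; 8,000 runs per distribution). It rejected in 5.5% of runs for normal, 4.9% for exponential and 5.5% for skewed bounded data. Type I error stays near 0.05, so the harm is the change of estimand.

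**The case against.** The strongest reply is that baseline is probably used already. The abstract defines the outcome as a change, so the natural reading of the analysis text is a change-score comparison, which subtracts FM0. This largely stands. It makes the change-score column the relevant one, and there the gain shrinks as r rises: 0.89 against 0.92 at r = 0.8. If f = 0.25 was meant on the change scale, ANCOVA gains still less at high r and does not bring power to 0.80. But subtracting FM0 is not the same as adjusting for it, and ANCOVA remains the more precise on either reading.

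It is also fair to say that randomisation keeps both unadjusted comparisons unbiased on average. A reader might infer that the planned estimate is biased; that holds only conditionally on the imbalance that actually occurs. Nor does choosing the test from the data inflate type I error.

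The age and gender sentence could be taken to mean that the primary analysis is adjusted. It sits with the fMRI methods and does not name FM0, so it does not answer the point.

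Three further inferences are tempting and not supported:
- **Wide baseline spread.** Time since stroke has no stated limit, but inclusion criterion 3 requires at least four of seven Jebsen-Taylor tasks, and no FMA-UE SD is given.
- **Dropouts ignored.** Quality control says that "the statistical processing principle of the data after the suspension of the clinical study will be determined", and a condensed article may leave the detail to the full plan.
- **Allocation not stratified.** The article's silence does not establish this.

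Finally, one might call the whole point a matter for the analysis plan. The article, however, names the primary test, so this is a stated choice and not an omitted detail.

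**Conclusion.** The point holds as a free improvement to a stated method, not as an invalidating flaw. On the likelier change-score reading, adjusting for FM0 adds 0.12, 0.07 and 0.03 to power at r = 0.5, 0.7 and 0.8 with d in SDs of the score, or 0.12, 0.07 and 0.04 with d in SDs of the change (differences of the unrounded powers). If follow-up scores are meant, the gain is much larger: from 0.52 to 0.64, 0.80 and 0.92. A reader might take that last comparison as the size of the loss, but the abstract's wording makes it the less likely case. All these sizes rest on the assumed r, a two-sided test, equal SDs and 33 evaluable per arm. The direction, with ANCOVA ahead, does not depend on which r between 0 and 1 is right. Separately, the data-driven choice of test leaves open whether the trial will report a mean difference or a rank comparison.

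**What to change.** In Data analysis, replace the FMA-UE sentence with a pre-specified ANCOVA: post-baseline FMA-UE on arm and FM0, reporting the adjusted mean difference with 95% CI. The estimated arm effect is the same whether the outcome is entered as the follow-up score or as the change from FM0, so this also settles the ambiguity between the abstract and the analysis text. If residuals are skewed or variances unequal, keep the same contrast and use robust or bootstrap standard errors instead of moving to Mann-Whitney. Apply the same baseline adjustment to FIM, BI and grip strength, each with its own baseline value. A mixed model over weeks 4 and 8, or further covariates such as age, are optional.

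The cost is wording only. The baseline values are already scheduled in Table 1, no patient or visit is added, and SPSS 25, the named software, fits ANCOVA.

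### The only image-level fMRI test described is before-versus-after within each arm, which does not answer the trial's between-arm question about VR and brain activation

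*Protocol article*

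**What the plan says.** The Introduction of the protocol article gives the primary goal as exploring how the VR intervention affects arm function and the associated brain activation. Under Interventions, both arms have 30 minutes of conventional rehabilitation; the VR arm adds 30 minutes of VR, and the control arm adds 30 minutes of upper-extremity exercise. fMRI is scheduled at baseline, week 4 and week 8.

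The Data analysis section treats the imaging in two places.

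- **Between arms, parameters.** The SPSS paragraph opens its comparative part with "The comparison between the groups will be carried out by the" and ends with an independent-sample t-test "for the parameter in FIM, BI, grip strength, fMRI and EEG at a" significance level given as a p-"value below 0.05".
- **Within arms, images.** After the SPM12 preprocessing steps, the next paragraph states: "Through an intragroup analysis, a paired" t-test "will be performed to assess brain alterations in each group (before and after the treatment". It then says that age and gender are taken into account, and that Pearson correlations will relate scale improvement to fMRI change. It describes no comparison of the arms on the images.

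The Imaging outcomes section defines what is sought as "changes in the BOLD effect in ipsilesional and contralesional M1 on the left and right hemispheres, and also EEG".

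**The concern.** An effect of VR is a difference between randomised arms. A paired test within one arm estimates everything that changed in that arm: VR, conventional therapy, any spontaneous recovery, familiarity with the scanner task and regression to the mean. The control arm shares all of these except VR, and has its own arm exercise in place of it.

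Two maps, one per arm, invite the reader to compare which regions reach significance in each. That is not a test of the difference. It can suggest a VR effect where there is none. It can also hide a real one when both arms are significant and VR changed more. At stake is the brain-activation part of the stated goal. The primary outcome, FMA-UE, is not affected.

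**Working it through.** **Inputs from the article.** 65 evaluable participants, 15% dropout, 78 recruited (Sample size). The enlarged figure reproduces: 65/0.85 = 76.5, so 77, and 66/0.85 = 77.6, so 78. It is used here only to set the arm size.

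**Assumptions.** 1:1 allocation (the ratio is not stated), hence about 33 evaluable per arm; two-sided tests at 0.05; the same true standardised change dz (mean change divided by SD of change) in both arms, so no VR effect; one region or parameter considered at a time.

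**Step 1: power of one paired test.** With n = 33, the power p is the probability that a noncentral F(1, n − 1) variable with noncentrality n·dz² exceeds the 5% critical value.

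**Step 2: the misleading pattern.** The arms are independent, so P(VR significant, control not) = p(1 − p).

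| True change in both arms, dz | p | p(1 − p) |
|---|---|---|
| 0.20 | 0.200 | 0.160 |
| 0.30 | 0.387 | 0.237 |
| 0.35 | 0.496 | 0.250 |
| 0.50 | 0.795 | 0.163 |
| 0.80 | 0.994 | 0.006 |

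In round figures, 50% power gives 0.5 × 0.5 = 0.25 and 80% power gives 0.8 × 0.2 = 0.16.

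**Step 3: the comparator.** Under the same equal change, a two-sided 5% test of the between-arm difference in change is significant in favour of VR with probability 0.05/2 = 0.025, whatever dz is.

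**Step 4: ratio.** 0.16/0.025 = 6.4 and 0.25/0.025 = 10, so the pattern arises about 6 to 10 times as often as the error of the proper test.

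**Step 5: very large changes.** At dz = 0.80 the pattern is rare (0.6%) because both arms are nearly always significant. The paired tests are then uninformative about VR for the opposite reason.

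**The case against.** The strongest reply is that the plan already has a randomised comparison of the imaging. The same section lists a between-group t-test for fMRI and EEG parameters, and the outcome definitions name both the region (M1) and the quantity (change in BOLD). The paired test is openly labelled intragroup, nothing says a VR effect will be inferred from it, and imaging is a secondary outcome.

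Much of this stands. A reader might infer that the trial has no way to show a VR effect on the brain; the planned between-group test rules that out. No paired test is described for EEG, so the within-arm criticism applies to the fMRI images only. What remains is that the between-group sentence does not say whether change or post-treatment values are compared, or which of two post-baseline visits is used, and that the images themselves get only the within-arm test.

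A reader might also infer that p < 0.05 will be applied voxel by voxel and produce many false activations. The documents do not support this. The 0.05 belongs to the between-group parameter tests, and the SPM12 paragraph prints no threshold. For EEG, "EEG data will be recorded at a sampling rate of 500 Hz from 17 silver electrodes" describes the recording; the article gives neither a number of frequency bands nor a rule that each electrode is tested separately. Map thresholds and multiplicity rules are details an article may leave to the full protocol or SAP, so their absence is not an error.

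Finally, one might quote 2p(1 − p), or 50 to 32%, as the misleading rate. Half of that is control significant and VR not, which nobody would read as a benefit of VR.

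**Conclusion.** The point holds for the image-level analysis. The article fixes a within-arm test where its own aim needs a between-arm one. This is a stated method that does not match the question, rather than a detail left out. Reading a VR effect from the two within-arm results would mislead about 16 to 25% of the time per region when there is none, against 2.5% for a between-arm test of change. Those figures rest on equal true change in both arms, 50 to 80% power per paired test, and two-sided 5% tests. With 33 per arm, that power corresponds to dz of about 0.35 to 0.50.

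The looseness of the between-group parameter test is a lesser, related point. The finding concerns secondary outcomes, but they carry the mechanistic half of the trial's goal, so it is worth correcting before the data are analysed. If the SAP, which is not shown, already has a group-by-time contrast on the images, the article and the SAP should be brought into line.

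**What to change.** 1. Make the image-level inference a two-sample VR-versus-control test on each patient's week-4-minus-baseline difference image (the group-by-time contrast), with age and gender as covariates.
2. State that the between-group t-tests on M1 BOLD and EEG parameters use change from baseline, and name the visit.
3. Keep the within-arm paired tests, labelled as descriptive, with no claim about VR resting on them.

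Stating how multiplicity is controlled for exploratory maps and EEG would also be advisable.

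The cost is a few lines of analysis text. The scans are already scheduled, SPM12 fits this model as standard, and no patients are added. The downside is fewer significant regions. With equal arms of n and equal SD s, the standard error of the between-arm difference is √(s²/n + s²/n) = √2 · s/√n, about 1.41 times that of a single arm, and change common to both arms cancels out.

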### Sample size

The objective of this study is to explore VR and conventional rehabilitation for upper extremity motor function after a stroke and to calculate the sample size by using G-Power (version 3.1) software. The effect size f is expected to be at least 0.25, and since the power is 0.80, the protocol should include 65 participants. Considering an expected 15% dropout rate, the sample size is increased to 78 participants.

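### Age and gender are promised in the analysis, but no named test carries a covariate, and the brain-behaviour correlation is left unadjusted for baseline severity and age

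*Protocol article*

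**What the plan says.** The Data analysis section of the protocol article names these tests:

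- chi-square or Fisher's exact test for counts;
- a t-test or Mann-Whitney U-test between arms for FMA-UE;
- an independent-sample t-test "for the parameter in FIM, BI, grip strength, fMRI and EEG at a" p-value threshold of 0.05;
- for imaging (software: SPM12), a paired t-test that "will be performed to assess brain alterations in each group (before and after the treatment");
- for the link between brain and behaviour: "The association between the improvement value of the correlation scales and the change in fMRI image data will be examined using the Pearson correlation coefficient".

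Between the last two stands one general sentence on covariates: "Age and gender will be taken into account as variables in the data analysis". It does not say which analysis or model it refers to. Baseline severity is not mentioned, nor is whether the correlation pools the arms or is run within each. No regression, analysis of covariance or partial correlation is named anywhere in the article.

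**The concern.** An adjustment is announced, but none of the listed tests can deliver it as named. This matters most for the correlation. Both of its variables are changes measured after baseline, so randomisation does not protect it. FMA-UE has a maximum of 66 points (Primary outcome), so the baseline score FM0 limits how much a patient can gain. Severity and age may also influence how much fMRI activation changes. A factor that drives both changes makes them correlate even if neither acts on the other.

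The Discussion part of the abstract presents the relation between upper extremity function and brain activation as what the study will provide evidence on, and the main Discussion wants such indices to help find patients who may benefit. An unadjusted r that is read as a direct link could mislead both uses.

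**Working it through.** The article gives no figure for this point, so there is none to reproduce. Three checks were made.

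**Inputs.** From Sample size: 65 evaluable patients and f = 0.25, which for two equal arms is d = 2 × 0.25 = 0.5. From Data analysis: the tests listed above, at the 0.05 level (two-sided assumed). The documents give no correlation of age or severity with either change, so values of 0.2, 0.3 and 0.4 are assumed.

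**1. Age and gender in the paired t-test.** Write the two scans of patient i as

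- before: m + b·age_i + c·gender_i + u_i + e_i1
- after: m + δ + b·age_i + c·gender_i + u_i + e_i2

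The difference is δ + e_i2 − e_i1. Age and gender have gone. In a simulated example with 33 patients, adding an age and gender effect to both scans left t = 2.0286 and p = 0.0509 unchanged. The patient-plus-time design has rank 34, and still 34 after the two columns are added. An age-by-time term raises it to 35. So the main effects cannot be estimated there, but age can enter as a modifier of the change, for example by regressing the change score on centred age.

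**2. A common cause behind the Pearson correlation.** Suppose one factor correlates a with both changes and there is no other link. Then:

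- expected r = a × a;
- chance of p<0.05, by Fisher's z: atanh(r) × √(65 − 3) = atanh(r) × 7.874, compared with ±1.96.

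| a (assumed) | expected r | shift in z | p<0.05, Fisher z | p<0.05, simulation (20,000 runs) | same, factor partialled out |
|---|---|---|---|---|---|
| 0.2 | 0.04 | 0.32 | 6% | 6.1% | 4.8% |
| 0.3 | 0.09 | 0.71 | 11% | 11.1% | 5.0% |
| 0.4 | 0.16 | 1.27 | 25% | 24.5% | 4.8% |

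With all 78 patients the simulated figures are 6.5%, 12.3% and 28.7%. The last column assumes that the factor is measured and is the one in the model.

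**3. Arm as the common cause.** If the arms are pooled and VR shifts both changes by d, then r = (d²/4)/(1 + d²/4). At d = 0.5 this is 0.0625/1.0625 = 0.059, and p<0.05 occurs in about 7% of trials of 65 (8% of 78). If the correlation is run within each arm, this source does not exist.

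**The case against.** **The covariate sentence is general.** A reader might infer that age and gender are meant for the paired t-test and that the adjustment is therefore void. The text does not say that. The sentence could be met by covariates in an SPM two-sample model or by a partial correlation, and the correlation is described in the very next sentence. This stands: what can be said is that no named test carries the covariates, not that they were put in the wrong one.

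**They do not always cancel.** Only the main effects do. A paired t-test is also a one-sample test of the change, and centred age and gender can enter a model for that change. In a simulation with 33 patients, a mean change of 0.4 SD and age correlating 0.3, 0.4 or 0.5 with the change, mean t rose from 2.33, 2.35 and 2.38 to 2.45, 2.57 and 2.75. This stands too.

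**An association is all that is claimed.** The article speaks of an association. If severity drives both changes, they are truly associated, and a significant r is not a false positive. This stands as a limit: the percentages above count errors only if r is read as a direct link.

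**Arm as a confounder.** A reader might count treatment arm as a major confounder. The text does not say that arms are pooled, the effect at d = 0.5 is small, and covariation produced by VR may be part of the mechanism under study.

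**Detail for an analysis plan.** Pooling and the form of the models may well be settled in a plan that is not shown. But the article commits itself to specific tests. A plan that adjusted would have to replace or extend them, and baseline severity is not among the covariates announced.

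**Conclusion.** The point holds in a limited form. The article announces age and gender, but none of its named tests uses them, and its brain-behaviour analysis is an unadjusted correlation of two post-baseline changes. Under assumed correlations of 0.2 to 0.4 between a common cause and both changes, the expected r is 0.04 to 0.16, and p<0.05 occurs in about 6% to 24-25% of trials with 65 patients without a direct link. At the low end this is close to the nominal 5%; the size depends on correlations that the documents do not give. Arm adds little at d = 0.5 (r about 0.06), and only if arms are pooled.

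A reader might go further and infer that the trial's main result is at risk. It is not: the randomised FMA-UE comparison does not depend on this correlation. The unadjusted between-arm t-test on M1 change is also protected from confounding by randomisation; there the gain from covariates is precision and a promise kept. This is a change worth making to a secondary, mechanistic analysis.

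**What to change.** 1. Keep the Pearson r as a descriptive figure. Make the main brain-behaviour analysis a linear regression or partial correlation of FMA-UE change on M1 change, adjusted for FM0, age and gender, and report it with a 95% CI. State whether arms are pooled; if they are, add arm.
2. Compare M1 change between arms by a linear model with arm, baseline M1, age and gender, in place of the unadjusted t-test.
3. Say in the covariate sentence that it refers to these two models. If the within-group analysis is also to use age and gender, state that they enter, centred, a model of the change score.

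All variables are collected already: demographics at enrolment, FMA-UE and fMRI at baseline (Table 1). With 65 patients the Pearson test has 65 − 2 = 63 degrees of freedom. The adjusted regression has 65 − 5 = 60, or 59 with arm. The between-arm model also goes from 63 to 60. The cost is three or four degrees of freedom and a change of wording.
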